Of the randomized controlled trials (RCTs) that have recently examined this issue [22-26], 4 have observed a regression to baseline behaviors after incentive removal [22-24,26] and only 1 has demonstrated persisting physical activity [25]. One reason for this may have to do with the limited application of health behavior change theories in the design of incentive programs [19]. It is increasingly suggested that for incentives to both stimulate and sustain health behavior change they should be grounded in theory [19,27,28]. In the single “positive” study, behavioral maintenance (ie, 16-week follow-up) was driven entirely by the lower active subgroup (ie, university students visiting the gym fewer than once per week at baseline)—possibly because exposure to the new behavior (ie, gym attendance) led to increased confidence to perform that behavior [25]. This presumption aligns well with self-determination theory, a global theory of motivation focused on the extent to which behaviors are done volitionally, which suggests that incentive programs designed to increase a person’s confidence are more likely to foster self-determined (or intrinsic) motivation [29,30]—a key driver of sustained physical activity [30].

Realizing the potential of incentives to promote sustained physical activity, therefore, will be contingent on research that improves the understanding of theoretical (eg, self-determined motivation) and contextual (eg, target group characteristics) factors that may influence incentive program effectiveness. The purpose of this protocol is to outline the design of an RCT that will examine the longer term effects of an existing physical activity promotion program that is enhanced by guaranteed incentives for lower active employees only in a real-world, ecological setting. We hypothesize that targeting lower active employees with incentives for tailored daily step goals (in addition to the generic, one-size-fits-all approach to goal setting that is typically used) may be more likely to create mastery experiences, increase confidence, and promote physical activity maintenance.

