### Standard Care Group

Standard care group participants will have access to Change4Life and will receive the standard minimal chance-based incentives (ie, less than 1 in 100 chance of earning Can $5 to $20 [US $3.70-$14.80] vouchers) for completing learning modules and health tasks. In addition, standard care participants will be asked to wear the accelerometer, which tracks steps and 10-minute bouts of MVPA per day, synchronize the device to the Change4Life program daily, and reach tailored daily step count goals for 10 weeks (weeks 3 to 12). Standard care participants will be instructed to increase their daily step counts by 1000 steps above their baseline average every 2 weeks until they reach the target goal of 3000 extra steps at week 7 (see Table 1). Change4Life will automatically calculate the average baseline value in the early hours of day 1, week 3 using data uploaded the previous 2 weeks (the Run-In period)—days with step counts less than 100 or greater than 50,000 will not be included in calculations [31]. This tailored and graded approach to setting step goals is more realistic than the traditional 10,000 step target (ie, the average Canadian adults accumulates only about 5000 steps per day) [32], may increase chances of intervention success (versus offering a lofty 10,000 step per day goal for everyone), and has worked well in employee populations in the past [33].

**Table 1 table1:** Daily step count goals across the Change4Life program.

Study week	Step count goal
Weeks 1-2	2-Week Run-In (to confirm lower active status and calculate daily step count average)
Weeks 3-4	Increase daily steps by 1000 above baseline average
Weeks 5-6	Increase daily steps by 2000 above baseline average
Weeks 7-8	Increase daily steps by 3000 above baseline average
Weeks 9-12	Maintain steps at 3000 above baseline average

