### Outcome Measures

The primary study outcome will be the mean proportion of participant-days that step goals are achieved during week 24 (the postintervention follow-up assessment period, T3). Mean proportion of participant-days that step goals are achieved during week 12 (intervention end point, T2) and volume of steps and 10-minute bouts of MVPA per week at T2 and T3 will be secondary outcomes. Physical activity will be objectively assessed using the StepsCount Piezo Rx accelerometer (StepsCount Inc, Deep River, ON, Canada). The Piezo Rx is a medical-grade device with a single axis piezoelectric sensor. This device has been found to be valid in calculating step counts and MVPA among adult participants [35,36]. Standard care and intervention participants will be encouraged to wear their accelerometer and synchronize it to the Change4Life program during the baseline 2-Week Run-In period (T1), as well as at the intervention end point (T2), and follow-up assessment (T3) with Can $10 (US $7.40) study retention vouchers; these vouchers for assessment completion will help minimize dropout and will not be contingent on step goal achievement.

The adherence outcome variables will be mean number of missing step count entries per week as well as mean number of Change4Life website log-ins in general. Participants’ self-determined motivation to exercise will be examined using the Behavioral Regulation to Exercise Questionnaire-3 (BREQ-3) [37,38]. Participants’ walking self-efficacy will be assessed using a modified version of the Self-Efficacy for Exercise Scale (SEE Scale) [39]. The BREQ-3 and the SEE Scale will be administered online at baseline (T1), intervention end point (T2), and during the follow-up assessment period (T3). The differential impact of the Can $1 (US $0.74) per day incentive on the various physical activity outcomes will be explored. For instance, we may find that while the guaranteed incentives stimulate step goal achievement at T2, they also undermine self-determined motivation and thus the prospect that people will continue to exercise after the incentive is removed.

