### Statistical Analyses

For each participant on each day of the study (participant-day level) continuous step count data will be obtained and screened for outliers (less than 100 steps per day, more than 50,000 steps per day) [31]. If participants did not synchronize their accelerometer for at least 3 separate workdays at T2 and T3, the last observation will be carried forward using T1 or T2 means [33]. This procedure conservatively assumes no change in variables and allows analysis by intention-to-treat. The step count data will then be dichotomized at the participant-day level to create a binary variable where participants achieved (value = 1) or did not achieve (value = 0) their step goal. Using this binary variable, the mean proportion of participant-days where step goals were achieved at week 24 will be compared.

SPSS version 21.0 (IBM Corp) will be used to fit a generalized linear model with participant random effects, a random intercept, time-fixed effects (T1-T3), and treatment-fixed effects (by study group). A binomial distribution with logit link for models using the binary outcome will be used to estimate the adjusted difference in the proportion of participant-days step goal achieved, and the bootstrap procedure and resampling of participants will be used to obtain 95% confidence intervals and *P* values. Comparisons across study groups will be adjusted for mean steps per day (baseline), age, gender, and income since these have moderated incentive-effects in the past [41]. The same procedures will be used to analyze T2 (ie, intervention end) binary data.

For continuous step count (ie, mean steps per day) and bout minutes (ie, total minutes of MVPA in 10-minute bouts per week) data at T2 and T3, a generalized linear model will be used, as above, except the difference in steps per day and MVPA bout minutes between groups will be obtained using least-squares means. Also, a repeated measures analysis of variance using linear mixed models with first order autoregressive covariance structures will be used to compare changes in self-determined motivation and self-efficacy between groups. Adherence will be analyzed using *t* tests comparing the mean number of missing step count entries per week and mean number of website log-ins per month between groups. This protocol is registered with ClinicalTrials.gov [NCT02638675].

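### The primary model as listed has no treatment-by-time term and includes the pre-randomization run-in, so it does not deliver the week-24 contrast that the outcome and sample size define

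*Protocol article*

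**What the plan says.** Outcome Measures fixes the time point: "The primary study outcome will be the mean proportion of participant-days that step goals are achieved during week 24". Week 12 (T2) is secondary. Sample Size is computed for week 24 as well, at 0.40 vs 0.20.

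Statistical Analyses states the matching intention, that "the mean proportion of participant-days where step goals were achieved at week 24 will be compared". It then specifies a binomial model with logit link, a participant-level random intercept and these fixed effects: "time-fixed effects (T1-T3), and treatment-fixed effects (by study group". The model is to "estimate the adjusted difference in the proportion of participant-days step goal achieved"; that sentence names no time point. Baseline mean steps, age, gender and income are covariates. For week 12 the section adds: "The same procedures will be used to analyze T2 (ie, intervention end) binary data".

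T1 is weeks 1 and 2. Table 1 gives that row as "2-Week Run-In (to confirm lower active status and calculate daily step count average", with no step goal. Randomization and Blinding places allocation after this period.

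**The concern.** The trial asks whether an effect survives 12 weeks after the incentive stops, so the analysis must be able to tell T3 from T2. A model with time and treatment terms but no product of the two assumes the same treatment odds ratio in every period. An effect that exists only at T2 would then feed the one coefficient that is read as the primary result, and could be reported as maintenance.

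This pattern is not remote. Of the five recent randomized trials discussed in the Introduction, "4 have observed a regression to baseline behaviors after incentive removal", and one showed persistence.

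T1 adds a second problem. No treatment effect is possible before allocation. The tailored goal is computed from the run-in data at the start of week 3, so goal attainment has no definition during the run-in itself.

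**Working it through.** **1. The plan's own figure.** Sample Size gives 79 per group for 0.40 vs 0.20, 80% power, two-sided 0.05. The unpooled formula for two proportions reproduces it:

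n = (1.960 + 0.842)² × (0.40×0.60 + 0.20×0.80) / 0.20² = 7.849 × 0.40 / 0.04 = 78.5, so 79 per group and 158 in total.

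This is a two-group comparison at week 24 alone.

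**2. What the listed model estimates.** For participant i, period t and group indicator G, leaving out covariates:

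logit P(goal met) = b_i + τ_t + β·G_i

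The group contrast on the log-odds scale is β at T1, β at T2 and β at T3. The week-24 contrast needs its own coefficient: β_t·G_i in place of β·G_i, with β_T3 as the target.

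**3. A rough size on the proportion scale.** If the true differences are 0 at T1, 0.20 at T2 and 0 at T3, a plain average is 0.20/3 = 0.067, or 0.20/2 = 0.10 over T2 and T3 only. The true week-24 difference is 0.

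**4. How often the pooled effect is significant when week 24 shows no effect.** Assumptions not in the document: 7 days per period, 79 per arm, T2 at 0.40 vs 0.20, T3 equal, random-intercept SD 1.2 to 2.5. Using each participant's average over the periods (4,000 simulated trials per scenario):

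- with T1 rows: 29 to 66%
- without T1 rows: 58 to 85%
- week-24 contrast: 5%

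**5. The same question with the logistic model itself.** Random-intercept logistic models were fitted by maximum likelihood, with intercept SD 1.5 and 7 days per period. Odds ratios and differences come from one large data set of 4,000 per arm. Rejection rates come from 200 trials of 79 per arm, using likelihood-ratio tests. The T1 rate is 0.10 in both arms unless stated.

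| True proportions, intervention vs standard care | Model as listed: OR; implied week-24 difference; rejection | T3 contrast with treatment-by-time: OR; difference; rejection |
|---|---|---|
| T2 0.40 vs 0.20; T3 0.20 vs 0.20 | 1.91; 0.077; 66% | 1.03; 0.004; 4% |
| T2 and T3 both 0.40 vs 0.20 | 2.91; 0.161; 99% | 3.69; 0.195; 99.5% |
| As above, T1 rate 0.20 | 2.66; 0.149; 95% | 3.89; 0.203; 99.5% |
| T2 0.60 vs 0.20; T3 0.40 vs 0.20 | 4.83; 0.232; 100% | 3.68; 0.192; 99.5% |

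With 200 trials, the simulation error of the 66% is √(0.66×0.34/200) = 3.3 percentage points. A further random-intercept logistic run of 300 trials gave 50 to 78% for the no-week-24-effect case.

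The last row shows that the bias can also run upward: a larger effect at T2 inflates the implied week-24 difference.

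**The case against.** The strongest reply is that the text shows a time-specific intention. It says that week-24 proportions will be compared, and the sentence giving T2 the same procedures would be empty if both periods shared one coefficient. A journal article may also condense its list of terms, and this one does not state that an interaction is excluded. This stands. A reader might infer that the plan never tests the week-24 question, or that it prescribes main effects only; the document supports neither. What remains is a conflict. If each analysis used a single week, a time effect over T1 to T3 would have no role. If all periods enter, the listed treatment term is pooled. The article gives link, distribution, random effects, time levels, covariates and bootstrap, so an analyst could reasonably follow the list as it stands.

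A second reply concerns T1. A reader might infer that a maintained difference of 0.20 would be cut by a third, since (0 + 0.20 + 0.20)/3 = 0.13. That figure needs binary T1 data, which have no definition, and it averages raw proportions where the plan uses a logit link. The logistic fit gives about 0.15 to 0.16, and only if some T1 rate is assumed. With T1 left out, a constant 0.20 is not attenuated at all. Nor is it a strong complaint that T1 serves as both response and covariate in the primary model, because baseline mean steps and daily goal attainment are different variables.

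Finally, none of the simulations includes the planned covariates, the carried-forward values or the participant bootstrap.

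**Conclusion.** The point holds in this form: the article states a week-24 comparison, but the model it lists, fitted as written, does not produce it. That model produces one odds ratio shared by T2 and T3, and by the run-in if T1 rows are given values. With an effect confined to the incentive period, the pooled term is significant in roughly 30 to 85% of trials, against about 5% for a T3-specific contrast.

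The range rests on assumed T2 rates of 0.40 vs 0.20, 7 days per period, the intercept SD, the T1 rate and whether T1 rows are included. The size moves with these assumptions. The mismatch itself does not depend on them, since it follows from the listed terms. It bears on the primary conclusion, so it should be settled before the analysts are unblinded.

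**What to change.** Restrict the binary response to T2 and T3. Keep baseline mean steps and the other named covariates, and add treatment-by-time. State that the primary test is the treatment contrast at T3, reported as a difference in mean proportion with the bootstrap interval already planned, and that the T2 contrast is secondary. Fitting week-24 data alone with the same covariates is an acceptable alternative; the T1-T3 time effect then drops out.

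Use the same structure for steps and MVPA. Their analysis is described for T2 and T3 but refers back to the model above, which leaves the role of T1 unclear.

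The cost is a wording change and one interaction parameter. No new data are needed, and the 158 stands because it is already a week-24 calculation. In the simulated maintained-effect cases the T3 contrast was significant at least as often as the pooled term (99.5% vs 99% and 95%).

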### Randomization and Blinding

Employees accumulating fewer than 10,000 steps per day during the baseline period (study weeks 1 and 2) will be randomized using a single, constant allocation ratio (1:1) to standard care or intervention groups. Randomization will occur using an online random number generator [40]. Participants will not be blinded to study group allocation. The research analysts will be blinded to group allocation until after the study is completed.

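### Fixing AR(1) for the three-occasion motivation and self-efficacy models can mis-state the standard error of baseline-to-follow-up change; an unstructured covariance avoids this at almost no cost

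*Protocol article*

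**What the plan says.** Under Outcome Measures, the two questionnaires have three occasions: "The BREQ-3 and the SEE Scale will be administered online at baseline (T1), intervention end point (T2), and during the follow-up assessment period (T3"). The timing comes from elsewhere in the Methods. Baseline is weeks 1 and 2 (Randomization and Blinding). T2 falls "during week 12 (intervention end point, T2") and T3 "during week 24 (the postintervention follow-up assessment period, T3").

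Under Statistical Analyses, the model is "a repeated measures analysis of variance using linear mixed models with first order autoregressive covariance structures", which "will be used to compare changes in self-determined motivation and self-efficacy between groups". No reason for the structure, no alternative and no robust standard error is given. The paragraph on the step-goal model in the same section names participant random effects and a random intercept. The sentence on motivation and self-efficacy names neither.

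Outcome Measures presents the effect of the incentive as something to be explored. Its example is that the incentive might raise step-goal achievement at T2, but that "they also undermine self-determined motivation" and so harm the prospect of continued exercise once it is withdrawn. No single motivation contrast is designated as the test of this.

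**The concern.** With three occasions, AR(1) has two parameters: one variance and one correlation. The T1–T3 correlation is not estimated. It is set to the square of the adjacent correlation. Questionnaire scores on motivation and confidence plausibly contain a part that stays with the person. In that case the T1–T3 correlation does not decay as fast as AR(1) requires, and the model overstates the variance of T1-to-T3 change.

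T3 is the only questionnaire taken after the incentive has stopped, so the baseline-to-T3 group difference is a natural summary of lasting harm or benefit to motivation. If its SE is inflated, real undermining is easier to miss, and a null result looks more reassuring than it should.

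**Working it through.** **Inputs from the article.** Three occasions; 79 per group (Sample Size); two-sided 5% level. The 79 is the plan's figure for the primary outcome, and it reproduces with unpooled variances: (0.4×0.6 + 0.2×0.8) × (1.960 + 0.842)² / 0.2² = 78.5, rounded up to 79. The article states no SE, SD, correlation or power for motivation or self-efficacy, so there is no plan figure to reproduce for this point.

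**Assumed inputs.** SD 1 at each occasion, complete data, separate group means at each time, AR(1) as the whole covariance, and a range of true correlations.

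**Step 1: what the AR(1) fit converges to.** The AR(1) likelihood uses the variances and the two adjacent covariances; the observed T1–T3 covariance does not enter. With equal variances and equal adjacent correlations ρ, the best-fitting AR(1) has correlation ρ and implies a T1–T3 correlation of ρ².

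**Step 2: SE of the group difference in T1-to-T3 change.**

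- True SE = √[2 × 2(1 − r₁₃)/79]
- Model SE = √[2 × 2(1 − ρ²)/79]
- Ratio = √[(1 − ρ²)/(1 − r₁₃)], which is √(1 + ρ) when r₁₃ = ρ

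Example at ρ = r₁₃ = 0.6: true SE = √(4×0.4/79) = 0.142; model SE = √(4×0.64/79) = 0.180; ratio = √1.6 = 1.265.

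**Step 3: results for T1-to-T3 change.** Power is for an effect that a correct SE would detect with 80% power.

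| True correlations (T1–T2 / T2–T3 / T1–T3) | SE ratio | Actual alpha | Power |
|---|---|---|---|
| 0.3 / 0.3 / 0.3 | 1.14 | 0.025 | 71% |
| 0.5 / 0.5 / 0.5 | 1.22 | 0.016 | 66% |
| 0.6 / 0.6 / 0.6 | 1.26 | 0.013 | 63% |
| 0.7 / 0.7 / 0.7 | 1.30 | 0.011 | 60% |
| 0.8 / 0.8 / 0.8 | 1.34 | 0.009 | 57% |
| 0.6 / 0.6 / 0.5 | 1.13 | 0.027 | 72% |
| 0.7 / 0.7 / 0.6 | 1.13 | 0.027 | 72% |
| 0.7 / 0.7 / 0.49 (true AR(1)) | 1.00 | 0.050 | 80% |
| 0.7 / 0.7 / 0.35 | 0.89 | 0.083 | 86% |

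The 86% in the last row is not a gain; it comes with an inflated type I error. In 1,500 simulated null trials per setting, the T1-to-T3 rejection rate was 0.015 at a common correlation of 0.5 and 0.013 at 0.7, in line with the formula.

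**Step 4: the other tests.** With equal adjacent correlations and equal variances, the T1–T2 and T2–T3 SE ratios are 1.00. They move only if the adjacent correlations differ: for 0.65 / 0.75 / 0.55 the ratios are 0.93 (T1–T2), 1.10 (T2–T3) and 1.07 (T1–T3). For the joint two-degree-of-freedom group-by-time test (large-sample, equal correlations of 0.3 to 0.8), actual alpha stays at about 0.04 to 0.05. Where the correct covariance gives 80% power, AR(1) gives 74% to 68% for an effect at T3 only or held at T2 and T3, and 82% to 86% for an effect at T2 only.

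**Step 5: spacing.** The gaps are about 10.5 and 12 weeks. If correlation decays in continuous time at 0.7 per 11.25 weeks, the ratios are 1.03 (T1–T2), 0.97 (T2–T3) and 1.00 (T1–T3). Unequal spacing is therefore not the issue; the imposed decay is.

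**The case against.** The strongest reply has four parts.

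- **The error is conditional.** A reader might infer that AR(1) will mis-state these error bars. The article does not support that: it gives no correlations, and Step 3 shows inflation, no error or the opposite error depending on them. This stands.
- **The contrast is not the plan's.** A reader might also infer that T1-to-T3 change is the designated test of undermining. It is not. The plan compares changes in a repeated-measures analysis, and its undermining example is worded around T2 with consequences after withdrawal. At a correlation of 0.6 the SE inflation equals losing 1 − 1/1.6 = 37.5% of the sample, but only for this one contrast under that one assumption. The joint test loses less. This stands too, though T3 remains the only post-withdrawal questionnaire.
- **A random intercept may be intended.** The wording does not exclude one beside AR(1) residuals, and it would largely remove the misfit. The neighbouring step-goal model names a random intercept and this one does not, so AR(1) alone is the more natural reading, but the text does not settle it.
- **Little rides on it.** Motivation and self-efficacy are neither the primary nor the listed secondary outcomes, AR(1) is a recognised choice for ordered and nearly evenly spaced measures, and with complete data the point estimates do not change. This fixes the severity as minor. It is not a reason to keep a restriction that three occasions and about 158 people do not need.

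**Conclusion.** The point holds in conditional form. If AR(1) is the whole covariance and scores have a stable person component, the model SE of the baseline-to-T3 group difference in change is about 13% to 34% too large. The upper part of that range is √(1 + ρ), or 14% to 34%, for equal correlations of 0.3 to 0.8. The 13% applies when the T1–T3 correlation is only 0.1 below adjacent correlations of 0.6 or 0.7. There is no error if the truth is AR(1), and the SE is too small (ratio about 0.89 for 0.7 / 0.7 / 0.35) if the T1–T3 correlation is below the square of the adjacent one. Under equal correlations the adjacent-occasion contrasts are unaffected.

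This is a minor point on an exploratory outcome, and the primary analysis is not touched. The article does not show that the planned analysis is invalid, or that undermining would be missed.

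**What to change.** In Statistical Analyses, replace AR(1) for motivation and self-efficacy with an unstructured covariance across T1, T2 and T3, with group, time and group-by-time effects. Report the group difference in T1-to-T3 change alongside the joint group-by-time test. Name a fallback if the model does not converge, such as compound symmetry, with robust standard errors where the software allows. If AR(1) was meant to sit beside a participant random intercept, say so.

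The cost is one model option and four more covariance parameters (six instead of two), which about 158 participants can support. No new data are needed, and neither the primary analysis nor the sample size changes.

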### Sample Size

Sample size calculations indicate that a final sample of 158 participants (79 per group) ensures 80% power (*P*<.05; 2-tailed) to detect a 0.20 difference in the mean proportion of participant-days step goals are reached between intervention and standard care groups for week 24 [24]. This calculation assumes that the mean proportion of participant-days step goal achieved in the intervention group in week 24 will be 0.40 (vs 0.20 in the standard care group) [24]. On the basis of data published by Patel et al [22] this difference translates into a relative effect size of 0.40. The participant enrollment target will be increased to 174 to account for a potential 10% dropout rate, a rate that has been reported by other similar studies [22,26].

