According to self-determination theory, incentives may help to build self-determined motivation primarily through their action on self-efficacy, especially for lower active people who exhibit fewer intrinsic motives to begin with (less motivation to crowd out) [44,45]. Regarding physical activity, one hypothesis is that incentives may increase a person’s self-efficacy to become more active by exposing them to a form of physical activity for the first time [29,30,44,45]. Especially if the activity is an achievable one (eg, walk 1000 more steps per day vs walk 10,000 steps per day), individuals may find their confidence to be more active increases after just a few weeks [29,30,44,45]. To align with self-determination theory, then, we decided to (1) target lower active employees only (because they have less/little self-determined motivation to crowd out) [23,24,29] and (2) offer incentives contingent on tailored/realistic step goal achievements (to maximize mastery experiences and increase self-efficacy) [45]. The main theoretical contribution of this protocol therefore is in its application of self-determination theory to the design of the incentive intervention (ie, realistic behavioral targets) and program evaluation (ie, tracking motivation throughout).

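### Comparing changes in motivation and self-efficacy without using the T1 score as a baseline gives up some precision on exploratory outcomes

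*Protocol article*

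**What the plan says.** Outcome Measures states that the two questionnaires "will be administered online at baseline (T1), intervention end point (T2), and during the follow-up assessment period (T3"). The same section places T1 in the two-week run-in. Randomization and Blinding allocates employees on their step counts from that run-in, so the T1 scores precede allocation.

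Statistical Analyses specifies a repeated measures linear mixed model with AR(1) covariance, which "will be used to compare changes in self-determined motivation and self-efficacy between groups". It does not say how T1 enters this model or which contrast is the result.

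The only covariate list is "Comparisons across study groups will be adjusted for mean steps per day (baseline), age, gender, and income". It stands in the paragraph on the binary step-goal outcome. Even if it is read as covering every group comparison, it does not include the T1 BREQ-3 or SEE score.

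The scales matter to the rationale. Outcome Measures gives, as an example of what might be found, that incentives raise step-goal achievement while "they also undermine self-determined motivation and thus the prospect that people will continue to exercise after the incentive is removed". The Discussion lists "program evaluation (ie, tracking motivation throughout") as part of the theoretical contribution.

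**The concern.** A repeated measures analysis that compares changes over three visits is normally fitted with all three visits as responses and a free mean for each arm at each visit. The group contrast in T1-to-T3 change is then the difference between arms in raw change scores.

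In a randomized trial the true T1 means are equal by design. Estimating them separately and subtracting them adds sampling noise and removes no bias. Using the T1 score as a baseline avoids that noise.

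At stake is the chance of detecting a real effect of the incentive on motivation or self-efficacy. The sample was sized for step-goal achievement, so no power is assured for these scales, and precision already available in the collected data is worth keeping.

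**Working it through.** **Inputs from the document.** 79 per group, two-sided 0.05, 1:1 allocation, scales at T1, T2 and T3, AR(1) covariance.

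**Assumed, because the document does not give them.** The correlation r between T1 and follow-up scores, shown over a range; equal SDs at each time; complete scale data for 79 per group; and a group difference of 0.40 SD. The article's relative effect size of 0.40 belongs to the primary outcome and is borrowed here only as an illustration.

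**The plan's own figure.** The article says "a final sample of 158 participants (79 per group) ensures 80% power" for 0.40 against 0.20. With unpooled variance: (1.960 + 0.842)² × (0.4×0.6 + 0.2×0.8) / 0.2² = 78.49, so 79 per group and 158 in total. The figure reproduces. It concerns the primary outcome; there is no corresponding figure for the scales.

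**Variances, in units of the scale variance.**
- Change contrast: v = 2(1−r)
- Adjusted for T1, or with a common T1 mean: v = 1−r²
- Ratio adjusted/change: (1−r²) / (2(1−r)) = (1+r)/2, so the reduction is (1−r)/2

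The standard error of a group difference is √(2v/79). The smallest difference detectable with 80% power is (1.960 + 0.842) × √(2v/79). Power for 0.40 SD is Φ(0.40/√(2v/79) − 1.96).

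Example at r = 0.5:
- Change: v = 1, SE = 0.159, 0.40/0.159 = 2.51, power Φ(0.55) = 0.71.
- Adjusted: v = 0.75, SE = 0.138, 0.40/0.138 = 2.90, power Φ(0.94) = 0.83.

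| r | Variance reduction | SE of change contrast larger by | Detectable difference (SD), change vs adjusted | Power at 0.40 SD, change vs adjusted |
|---|---|---|---|---|
| 0.3 | 35% | 24% | 0.527 vs 0.425 | 57% vs 75% |
| 0.5 | 25% | 15% | 0.446 vs 0.386 | 71% vs 83% |
| 0.7 | 15% | 8% | 0.345 vs 0.318 | 90% vs 94% |
| 0.8 | 10% | 5% | 0.282 vs 0.267 | 98% vs 99% |

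Below r = 0.5, 2(1−r) exceeds 1, so the change contrast is less precise than comparing follow-up scores and ignoring T1.

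**Under the planned AR(1) structure.** The T1–T3 correlation is the square of the adjacent-visit correlation. Exact generalized least squares for three visits and 79 per group compared free T1 means per arm with a common T1 mean:

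| Adjacent correlation | T2 variance ratio | T3 variance ratio | T3 SE, change vs common T1 mean |
|---|---|---|---|
| 0.5 | 0.750 | 0.625 | 0.1949 vs 0.1541 |
| 0.7 | 0.850 | 0.745 | 0.1607 vs 0.1387 |
| 0.8 | 0.900 | 0.820 | 0.1350 vs 0.1223 |

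These ratios agree with (1+r)/2 at the correlation for each visit. At an adjacent correlation of 0.7 the T1–T3 correlation is 0.49, and power for 0.40 SD at T3 is about 70% against 82%.

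**The case against.** The strongest reply is that nothing here is wrong. A group-by-time comparison in a mixed model is a standard randomized analysis. It is unbiased, and this choice leaves the type I error alone. That stands: the point is efficiency only.

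The role of T1 is also inferred. A reader might take the article as stating that T1 is an outcome and not a covariate, but it says neither, and a condensed article may leave such detail to the full plan. What remains is that the article does fix the type of model and the comparison of changes, and on the ordinary reading these make T1 a response. The point questions that choice and does not complain of missing detail.

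The importance is easily overstated. A reader might infer that undermined motivation is the trial's key risk and that tracking it is the main contribution. The Discussion calls it one of several risks and makes tracking only part of the contribution. BREQ-3 and SEE are named neither as primary nor as secondary outcomes, and the differential impact of the incentive is to be explored. Nor does the article say that a null result would be taken as absence of undermining.

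Finally, the size depends on r. At r = 0.8 and a 0.40 SD difference, the gain is about one percentage point of power. That also stands, and is why a range is shown.

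**Conclusion.** The point holds as a free improvement to an exploratory analysis. On the ordinary reading, the stated comparison of changes is valid but less precise than one that uses the pre-randomization T1 score, by a variance factor of (1+r)/2. The loss is material at r of 0.5 or below, where the standard error is at least 15% larger. It is small at r of 0.8 or above, where the standard error is about 5% larger or less. If AR(1) is true, the loss is greater at T3, the visit after the incentive has ended, than at T2.

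The figures rest on an assumed r, equal SDs over time, complete data, a normal approximation and a borrowed 0.40 SD difference. The primary analysis, the sample size and the secondary activity outcomes are unaffected. The documents do not support a claim of bias or of an invalid test.

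**What to change.** In Statistical Analyses, state how T1 enters the BREQ-3 and SEE model, in one of two ways:

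- Preferred: keep T1, T2 and T3 as responses, but constrain the two arms to a common T1 mean, with separate group effects at T2 and T3.
- Alternative: take T2 and T3 as the responses, with group, time, group-by-time, the participant's own T1 score and T1-by-time.

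In either case, name the adjusted group differences at T2 and T3 as the reported results.

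The two should not be treated as interchangeable when data are missing. The second drops participants without a T1 score and takes nothing from those with T1 only; the first retains both. That matters here because Limitations expects that dropout could be substantial.

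The cost is a sentence or two of analysis wording. It needs no new data, no extra participants and no change of software.
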